## Abstract

**Background::**

Hemorrhoids are a common and seriously disruptive condition that seriously affects people's lives in terms of treatment. Injection therapy is an effective minimally invasive scheme for the treatment of grade II–III hemorrhoids, but its clinical application is limited by the adverse reactions caused by injection drugs. Some clinical studies have confirmed the efficacy and safety of Shaobei injection as a traditional Chinese medicine extract. However, there is no standard randomized controlled study to verify its efficacy and explore its potential mechanism.

**Methods::**

This is a prospective, randomized, single blind, parallel controlled trial to study the efficacy of Shaobei injection in the treatment of grade II–III hemorrhoids and its effect on the expression of fibulin-3 and fibulin-5 in fibulin protein family. The patients will be randomly divided into a treatment group and control group. The treatment group will be treated with Shaobei injection, and the control group will be treated with rubber band ligation. The observation indexes include: visual analysis scale, postoperative hospital stay, total use of painkillers, fibulin-3 and fibulin-5, hemorrhoids recurrence, and adverse events. Finally, the data will be statistically analyzed by SPASS 18.0 software.

**Discussion::**

This study will compare the efficacy of Shaobei injection with the rubber band ligation method in the treatment of grade II–III haemorrhoids and investigate its effect on the expression of fibulin-3 and fibulin-5 in the fibulin protein family. The results of this study will provide a basis for the clinical use of Paeoniflora injection as an alternative to traditional sclerosing agent in the treatment of grade II–III haemorrhoids.

**Trial registration:** OSF Registration number:DOI 10.17605/OSF.IO/MKVDB

## Introduction

1

Hemorrhoids are a common clinical disease. At present, the exact prevalence of hemorrhoids is not clear, as most patients have no obvious symptoms in the early stages and do not seek treatment from doctors.^[1]^ A study of patients who underwent routine colorectal cancer screening found that 39% of patients had hemorrhoids, with 55% of these patients reporting no symptoms.^[2]^ Hemorrhoids are more common in people aged 45 to 65 years.^[3]^ Although the exact etiology of hemorrhoids is not clear, hemorrhoids are related to the increase of hemorrhoid venous plexus pressure, such as defecation tension secondary to constipation.^[1]^ Other related factors include obesity, pregnancy, chronic diarrhea, anal sex, cirrhotic ascites, pelvic floor dysfunction, and low fiber diet.^[3,4]^ Although most people have no obvious symptoms in the early stages, as the disease progresses, patients will have to bleed, swelling, prolapse, pain, pruritus and anal discomfort, which seriously affect the quality of life of patients. In addition, repeated bleeding can lead to secondary anemia, hemorrhoids sometimes lead to massive bleeding, requiring emergency hospitalization, and blood transfusion.^[5,6]^

At present, there are many treatment schemes for hemorrhoids, which can be divided into conservative treatment and surgical treatment. Surgical treatment includes rubber band ligation (RBL), injection therapy, hemorrhoidectomy, stapler hemorrhoidectomy etc.^[7]^ For grade II–III hemorrhoids, people prefer minimally invasive surgery, because it means less trauma and shorter recovery time.^[8]^ RBL is recognized as a safe and effective minimally invasive technique. It is one of the most common and simplest minimally invasive therapies for the treatment of symptomatic early hemorrhoids. The literature reports that the recurrence rate of this scheme in the short term is between 12% and 18%, but in the long-term follow-up, up to 42% of patients have intermittent residual symptoms, such as bleeding, pruritus, and anal lump.^[9]^ Therefore, there is still a need to continue to explore a more optimized minimally invasive surgical option.

Injection therapy is another minimally invasive scheme. However, the hardeners used in traditional injection therapy are accompanied by the risks of thrombosis, local tissue ischemia or necrosis, bleeding, and so on. These adverse events limit the clinical application of injection therapy.^[10–12]^ Shaobei injection is a traditional Chinese medicine injection, which is extracted from Wu Mei (Fructus Mume), Wu Bei Zi (*Galla Chinensis*) and Chi Shao (*Radix Paeoniae Rubra*). It can soften and shrink hemorrhoids, inhibit inflammatory reaction and improve pain.^[13]^ In the Chinese hemorrhoid diagnosis and treatment guidelines, Shaobei injection is recommended for the treatment of grade I–III hemorrhoids.^[7,14]^ A retrospective study found that Shaobei injection is effective and safe in the treatment of grade II–III hemorrhoids. Compared with RBL, it has more advantages in reducing postoperative adverse events, hospitalization expenses and the length of time.^[15]^ There is still a lack of prospective clinical studies to validate this conclusion as to whether Shaobei injection is superior to RBL in the treatment of grade II–III haemorrhoids.

In recent years, the mechanism of pathological changes in the anal pad based on elastic fiber lesions has attracted increasing attention, and the relationship between the occurrence and development of hemorrhoids and elastic fibers has attracted more and more attention.^[16]^ The expression of fibulin protein family plays an important role in the formation and metabolism of elastic fibers. Fibulin-3 can form and stabilize basement membrane, elastic fibers, and loose connective tissue.^[17]^ Fibulin-5 not only acts on the synthesis of elastic fibers, but also inhibits neovascularisation.^[18]^ This study will take the classic RBL as the control, through a prospective randomized controlled experiment to explore the efficacy and safety of Shaobei injection in the treatment of grade II–III hemorrhoids, evaluate its effect on the expression of fibulin-3 and fibulin-5 in fibulin protein family, and explore the potential mechanism of Shaobei injection in the treatment of hemorrhoids.

## Materials and methods

2

### Study design

2.1

This is a prospective, randomized, single blind, parallel controlled trial to study the efficacy of Shaobei injection in the treatment of grade II–III hemorrhoids and its effect on fibulin protein expression. Participants will be randomly divided into a treatment group and control group. The treatment group will receive Shaobei injection and the control group will receive RBL. They will be followed up for 6 months after treatment. Flow diagram is shown in Figure 1. This research scheme follows the latest consolidated standards of reporting trials 2017 and Standard Protocol Items: Recommendations for Interactive Trials 2013 statement.

**Figure 1 F1:**
[figure not shown]
Flow diagram.

### Ethics and registration

2.2

This research plan has been reviewed and approved by our Clinical Research Ethics Committee and will be conducted in strict accordance with the Declaration of Helsinki and Ethical guidelines for Clinical Research, and be supervised by the Ethics Committee. This protocol has been registered in the open science framework (Registration Number: DOI 10.17605/OSF.IO/MKVDB). Patients will be informed in detail of the purpose, plan, and potential risks of the study before the study begins and will sign a written informed consent form after they have agreed to participate in the study.

### Patients

2.3

#### Diagnostic basis

2.3.1

For the diagnosis of hemorrhoids, refer to the Guidelines for diagnosis and treatment of hemorrhoids in China (2020),^[7]^ and its classification adopts Goligher classification.^[19]^

#### Inclusion criteria

2.3.2

(1)Symptomatic grade II or III hemorrhoids diagnosed during preoperative evaluation;(2)Age ≥18 years and ≤70 years;(3)The subjects will agree to join the study and sign the informed consent form.

#### Exclusion criteria

2.3.3

(1)History of hemorrhoid surgery or perianal surgery, with a surgical anastomosis less than 3 cm from the dentate line;(2)Fecal incontinence or dysdefecation syndrome resistant to drugs;(3)Combination of other anal diseases (such as anal fissure, anal fistula, etc);(4)Irritable bowel syndrome with severe constipation or diarrhea;(5)The presence of any condition that contraindicated surgery;(6)Pregnant or lactating women.

#### Abscission criteria and treatment

2.3.4

(1)Those who have a preoperative contraindication to surgery or an intraoperative emergency that, in the judgement of the investigator, warrants discontinuation of the trial and appropriate life-saving treatment;(2)Those who cannot continue to participate in the study due to subjective or objective factors;(3)Those who lose many visits and are unable to contact during the follow-up;(4)Those who are misdiagnosed or accidentally included because they did not meet the inclusion and exclusion criteria.

For the withdrawal or loss of follow-up cases, the researchers should actively take measures to complete the last test as far as possible, so as to analyze its efficacy and safety, and take corresponding treatment measures. All dropped cases should be reported on the case report form (CRF) for the reason for the dropout.

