### Sample size

2.4

The calculation of sample size is based on the mean and standard deviation of visual analogue scale (VAS) scores at rest 24 hours after operation. According to the results of the pilot study, the sample size in the treatment group is 3.71 ± 1.67 and that in the control group is 4.61 ± 1.47. Set up α = 0.025, 1-sided test, β= 0.10. It is calculated by PASS 15.0 software that 66 participants are needed in each group, and the estimated withdrawal rate is 10%. So 74 patients will be included in each group.

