### Randomization and blinding

2.5

We will randomly assign patients who meet the criteria for the treatment group (Shaobei injection group) or the control group (RBL group) in a ratio of 1:1 through a central network-based randomization tool. Random numbers will be generated by independent statisticians who do not participate in the test implementation or statistical analysis with SAS 9.3 software (SAS Institute, Cary, NC). Put the random number into an opaque and sealed envelope, and the patients who meet the standard randomly select the envelope to obtain the random number inside to complete the grouping. Limited by way of intervention, surgeons will know the results of grouping, while patients, anesthesiologists, data analysts, and other research assistants will not know the results of grouping.

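### Section 2.3.4 makes an intraoperative emergency, and ineligibility found at any time, a ground for leaving the trial, so later outcomes of randomised patients can be lost selectively

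*Protocol article*

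**What the plan says.** Section 2.3.4 of the protocol article gives four grounds for dropping out. Criterion (1) covers a contraindication found before surgery and "an intraoperative emergency that, in the judgement of the investigator, warrants discontinuation of the trial". Criterion (2) is open-ended: "Those who cannot continue to participate in the study due to subjective or objective factors". Criterion (3) covers patients who miss many visits and cannot be reached. Criterion (4) reads "Those who are misdiagnosed or accidentally included because they did not meet the inclusion and exclusion criteria".

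For withdrawn or lost cases, "the researchers should actively take measures to complete the last test as far as possible, so as to analyze its efficacy and safety". The section adds: "All dropped cases should be reported on the case report form (CRF) for the reason for the dropout".

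On blinding, section 2.5 states that "surgeons will know the results of grouping", "while patients, anesthesiologists, data analysts, and other research assistants will not know the results of grouping". Section 2.6 has one surgeon operate on every patient in both arms. Section 2.8 has two researchers, blind to arm, collect adverse events throughout the study.

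Section 2.4 states that "66 participants are needed in each group, and the estimated withdrawal rate is 10" per cent, which gives 74 enrolled per arm. Section 2.7 schedules resting VAS from 4 to 48 hours, defecation VAS to day 7, tablet use over 7 days, hospital stay, and recurrence at 1, 3 and 6 months.

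**The concern.** Criterion (1) treats stopping the procedure and leaving the trial as one event. An emergency during injection or ligation comes after allocation, may result from the procedure being tested, and arises when the operator knows the arm. If such patients leave with at most one further test, most of the section 2.7 schedule may never be recorded for them. An analysis set defined later cannot restore data that were not collected.

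Criterion (4) has a related weakness. It sets no limit on when ineligibility may be found and does not say who decides. Both procedures begin with an endoscopic inspection of the haemorrhoids (sections 2.6.1 and 2.6.2), so a misdiagnosis could come to light when the operator already knows the arm.

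What is at stake is the comparability of the arms. If patients with poor courses are lost more often from one arm, that arm looks better than it should on pain, tablets, stay and recurrence.

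**Working it through.** **Step 1: the plan's own figure.** Section 2.4 gives 24-hour resting VAS of 3.71 (SD 1.67) against 4.61 (SD 1.47), one-sided α 0.025 and β 0.10.

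- Planned difference: 4.61 − 3.71 = 0.90.
- Root-mean-square SD: √((1.67² + 1.47²)/2) = 1.573.
- Exact two-sample t test: power is 0.8992 with 65 per arm and 0.9036 with 66, so 66 are needed, as stated.
- Inflation for 10% withdrawal: 66/0.90 = 73.3, rounded up to 74, as stated.

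The stated sample size reproduces, and the point made here does not change it. The allowance is 74 − 66 = 8 patients per arm (8/74 = 10.8%).

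**Step 2: when each criterion can act, and who judges.**

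- Intraoperative emergency, criterion (1): always after allocation. The call belongs to the investigator, who is not identified and need not be blind. The surgeon is unblinded.
- Preoperative contraindication, criterion (1): before treatment. Section 2.3.3 already excludes conditions that contraindicate surgery, and section 2.5 randomises patients who meet the criteria. A contraindication that still leads to a drop was therefore found after screening was passed, possibly after randomisation. The text does not say.
- Ineligibility, criterion (4): at any time, with no decision-maker named.

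**Step 3: what is still collected.** The last-test sentence names withdrawn and lost cases, asks for one test, and is not binding. Section 2.7 needs four resting VAS scores, four defecation scores, a 7-day tablet count, hospital stay and three follow-up visits. One test cannot supply these.

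**Step 4: possible size.** Suppose the 24-hour scores of k patients out of 74 in one arm are lost, and would have averaged h points above the rest of that arm, in the pilot's units. The observed arm mean is then too low by k × h/74. The documents give neither k nor h, so both are assumptions:

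| k lost in one arm | h (points) | Shift = k × h/74 | Share of 0.90 |
|---|---|---|---|
| 1 | 2 | 0.027 | 3% |
| 4 | 3 | 0.162 | 18% |
| 8 (whole allowance) | 4 | 0.432 | 48% |

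Losses in the Shaobei arm would widen the apparent benefit, and losses in the ligation arm would narrow it. Similar losses in both arms would largely cancel.

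**The case against.** The strongest objection is that nothing in the article removes these patients from the analysis. The purpose given for the last test is to analyse efficacy and safety. Section 2.10 names no restricted population, and analysis sets are commonly defined in a full protocol or SAP that is not shown. This stands. A reader might infer from section 2.3.4 that dropped cases are excluded, but the text does not say so. Nor does the step from 66 to 74 show it: such an allowance is routine even when everyone randomised is to be analysed, because some endpoint values will be missing.

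A reader might also infer that an unblinded team decides who leaves. That is too strong. Section 2.5 unblinds surgeons only, the judgement clause belongs to criterion (1) alone, and the investigator is not said to be the surgeon. What can be said is that the person judging may be the surgeon and that nothing requires otherwise.

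A third inference would be that emergencies disappear from the safety comparison. Section 2.8 points the other way: blinded staff collect adverse manifestations during the study and all events go on the CRF, as does the reason for dropping out. No figure for hidden adverse events can be supported.

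Finally, a preoperative contraindication is not a treatment failure, and criterion (1) concerns events serious enough to need life-saving care, which may be rare. Both points are fair, and the second favours the lower end of the range.

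The objection does not answer the loss of data. A discretionary event after randomisation, possibly caused by the procedure, is a stated ground for leaving, and the only safeguard is one test where feasible.

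**Conclusion.** The concern holds as a defect in the stated withdrawal rule. It is not a finding that patients are excluded from the analysis or that adverse events go uncounted. Section 2.3.4 lets randomised patients leave for a reason that may be caused by the assigned procedure and may be judged with knowledge of the arm, and it lets ineligible patients be dropped with no time limit. Outcomes from 24 hours to 6 months can then be lost selectively.

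The size of any bias is unknown because no emergency rate is given. The range of 3% to 48% of the planned 0.90 difference rests on assumed numbers of patients and assumed excess pain, with all losses in one arm. The upper end uses the full allowance of 8 patients and is an extreme case. The sample size of 66, inflated to 74, is unaffected. The change is worth making because it is specific, cheap and protects the comparison.

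**What to change.** Reword section 2.3.4, with a matching line in section 2.5, to state that:

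1. Criterion (1) ends the study procedure but not follow-up. The clinical decision to stop is left as it is.
2. Unless consent is withdrawn, all randomised patients are followed for VAS, tablets, stay and recurrence and compared in their assigned arm. Criterion (2) cannot be recast as a mere procedure stop, since it concerns people unable to continue in the study. The rule therefore covers those who still consent, and patients who cannot be reached are recorded as missing.
3. Every patient whose procedure was started counts in the safety comparison, including intraoperative emergencies.
4. Contraindication and eligibility checks are completed before the envelope is opened.
5. Criterion (4), the one exception to item 2, applies only to facts that predate randomisation and is judged by an existing member of staff who is blind to arm.

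The cost is protocol wording, re-approval by the ethics committee as section 2.9 requires for any change, and a few extra patient contacts. The downside is slight dilution of the estimated effect, because patients who did not complete the procedure stay in their arm.

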### Sample size

2.4

The calculation of sample size is based on the mean and standard deviation of visual analogue scale (VAS) scores at rest 24 hours after operation. According to the results of the pilot study, the sample size in the treatment group is 3.71 ± 1.67 and that in the control group is 4.61 ± 1.47. Set up α = 0.025, 1-sided test, β= 0.10. It is calculated by PASS 15.0 software that 66 participants are needed in each group, and the estimated withdrawal rate is 10%. So 74 patients will be included in each group.

### Randomization and blinding

2.5

We will randomly assign patients who meet the criteria for the treatment group (Shaobei injection group) or the control group (RBL group) in a ratio of 1:1 through a central network-based randomization tool. Random numbers will be generated by independent statisticians who do not participate in the test implementation or statistical analysis with SAS 9.3 software (SAS Institute, Cary, NC). Put the random number into an opaque and sealed envelope, and the patients who meet the standard randomly select the envelope to obtain the random number inside to complete the grouping. Limited by way of intervention, surgeons will know the results of grouping, while patients, anesthesiologists, data analysts, and other research assistants will not know the results of grouping.

### Interventions

2.6

In order to ensure the consistency of surgical techniques, all patients will be operated by the same surgeon. All patients will use a unified anesthesia scheme. Patients will take the stone position and the surgical site is routinely disinfected. Except for different surgical methods, other treatment schemes are the same.

#### Treatment group

2.6.1

Shaobei injection (Taifeng Biotechnology Co., Ltd., Henan, China) will be mixed with 1% lidocaine hydrochloride in the volume ratio of 1:1 to prepare injection medicine. Distribution of the hemorrhoid nucleus will be probed under the anoscope to determine the injection site and injected according to the nucleus from small to large. Firstly, 2 mL will be injected under the supra-mucosa of hemorrhoids, and then the needle is injected at the highest point in the center of hemorrhoids. When a feeling of muscular resistance appears, the needle is slowly withdrawn and the prepared injection solution of peony is injected until the haemorrhoid nucleus is full and filled, then gently massage with gauze for 30 seconds, and compressed to stop bleeding. Each haemorrhoid is injected with 3 to 5 mL depending on the size of the haemorrhoid.

#### Control group

2.6.2

Anal endoscopy will be used to explore the distribution of hemorrhoids, determine the location of ligation hemorrhoids, place the ligation anal endoscope, connect the tail end of the ligation device with the negative pressure aspirator, adjust the negative pressure value of the aspirator to 100 kPa, open the ligation device, inhale the hemorrhoid tissue into the tube, check to ensure that there is no air leakage, tight the elastic line, release the negative pressure suction, and exit the ligation device.

The 2 groups of patients will be wrapped with the same dressing after operation, and the same nursing scheme is adopted after operation. When the pain is unbearable, the patients will be given 0.1 g of nimesulide dispersible tablets orally (Wuhan Changming pharmaceutical, China, GMP H20010730), and the use will be recorded.

### Outcomes

2.7

(1)The VAS^[20]^ will be used to evaluate patients’ pain changes. The VAS is often used to measure pain intensity.^[21]^ Patients will be asked to mark a point between 0 and 100, where 100 indicate maximum pain (rightmost end) and 0 indicates no pain (leftmost end). VAS scores at rest will be recorded at 4 hours, 12 hours, 24 hours, and 48 hours after operation for both groups. VAS score of patients during defecation will be recorded on the 1st, 2nd, 3^rd^, and 7th day after operation;(2)The total amount of nimesulide dispersible tablets (tablets) will be taken orally within 7 days after operation;(3)The patient's postoperative stay in hospital (define as the day of operation started to the key of discharge);(4)In the first month of postoperative follow-up, the anal pad tissue samples of the patient will be collected according to the wishes of the patient, and fibulin-3 and fibulin-5 in fibulin protein family will be detected by Western blot;(5)The patients will be followed up in the first month, the third month and the sixth month after operation. The healing or recurrence of hemorrhoids will be evaluated by rectal endoscopy and patient symptoms (including pain, pruritus, bleeding, etc).

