### Safety evaluation

2.8

We will measure blood routine, urine routine, electrocardiogram, liver function, and renal function at baseline and after treatment to evaluate the safety of treatment. Two dedicated researchers will collect any adverse manifestations of patients during the study, including skin pruritus, swelling, necrosis, abnormal bleeding, etc. The details of all adverse events will be recorded in the CRF. The adverse reactions of the 2 groups of patients will be counted at the end of the study. The 2 researchers are unaware of the grouping results.

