### Statistical analysis

2.10

The data from this study will be statistically analyzed by independent statisticians through SPSS 18.0 software. The Chi square test will be used for counting data; the mean ± standard deviation ($\bar{\text{x}}\pm \text{s}$) will be used for the measurement data, the independent sample *t* test will be used for the normal distribution, and the Mann–Whitney *U* test will be used for the skew distribution. When *P* < .05, the difference will be considered to be statistically significant.

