There are also some deficiencies in this study: firstly, due to the limitations of intervention measures, this study cannot be double-blind, which may cause bias to the results; Secondly, although our follow-up time is 6 months, it may not be enough to pay attention to the recurrence indicators of patients; Thirdly, we need to detect the expression of fibulin-5 protein by taking the tissue expression of anal pad again, which may lead to the loss of follow-up of some patients.

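### Fibulin tissue is taken in the first month only from patients who wish it, so the groups compared may not be the randomised groups and a difference cannot be safely attributed to treatment

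*Protocol article*

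**What the plan says.** The Abstract (Methods) sets out to study the efficacy of Shaobei injection and "its effect on the expression of fibulin-3 and fibulin-5 in fibulin protein family". Study design (2.1) repeats this aim. The Introduction and Discussion describe it as exploring a potential mechanism.

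Outcomes (2.7), item (4), gives the sampling rule. On timing: "In the first month of postoperative follow-up, the anal pad tissue samples of the patient will be collected". On who is sampled: "the anal pad tissue samples of the patient will be collected according to the wishes of the patient". It gives no expected share and does not say when the wish is recorded. It describes no pre-treatment tissue sample, whereas Safety evaluation (2.8) states baseline measurement for its own tests: "We will measure blood routine, urine routine, electrocardiogram, liver function, and renal function at baseline and after treatment".

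For measurement data, Statistical analysis (2.10) says that "the independent sample *t* test will be used for the normal distribution", with the Mann–Whitney test for skewed data. No other method is named for fibulin.

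The limitations paragraph of the Discussion says that fibulin-5 needs "taking the tissue expression of anal pad again, which may lead to the loss of follow-up of some patients". It does not mention selection of the patients who give tissue.

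**The concern.** Randomisation protects a comparison only while the patients compared are those randomised, or a subset fixed without regard to what happened after allocation. If willingness is settled around the month 1 visit, the patient already knows how much pain, bleeding or residual swelling there has been.

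The trial itself expects the arms to differ in such experience. The pilot figures in Sample size (2.4) show different pain at 24 hours, and the Introduction cites fewer postoperative adverse events with the injection. If symptoms influence willingness and tissue state is related to fibulin, an arm difference could partly reflect who volunteered. It would nevertheless be read as an effect of treatment and as evidence of mechanism.

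**Working it through.** **The plan's own figure.** No number is stated for fibulin. The sample size is based on 24-hour resting VAS, and it reproduces. The difference is 4.61 − 3.71 = 0.90 and the mean variance is (1.67² + 1.47²)/2 = 2.475 (SD 1.573). With one-sided α = 0.025 and 90% power, n = 2 × (1.960 + 1.282)² × 2.475 / 0.90² = 64.2, so 65 by the normal approximation. The noncentral t gives 89.9% power at 65 and 90.4% at 66, so 66 is right. Then 66/0.90 = 73.3, so 74 enrolled. This calculation does not cover fibulin. It is used here only for the 74 per arm, allocated "in a ratio of 1:1 through a central network-based randomization tool".

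**Is a subset comparison at risk?** Four statements combine:
- sampling is optional (2.7);
- it happens after treatment (2.7);
- the only tests named are unadjusted (2.10);
- patients do not know their group (2.5), but blinding to allocation does not hide a patient's own symptoms.

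The risk therefore follows from the stated rule. Its size does not, because the documents give no uptake and no link between symptoms and fibulin. The two calculations below rest on assumed inputs.

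**Range A: differential uptake, no true effect.** Assume willingness depends on a post-treatment state with correlation ρ to fibulin, and a share p of each arm opts in from one end of that state. The shift in mean fibulin among those sampled is ρ × m(p) in SD units, where m(p) = φ(z)/p and z is the normal quantile at 1 − p. The spurious arm difference is ρ × [m(p₁) − m(p₂)]. The type I error uses SE = √(1/74p₁ + 1/74p₂), taking the SD as 1 in each sampled group, and a two-sided 5% test.

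| Uptake by arm | m(p₁), m(p₂) | Difference, ρ = 0.3 | Difference, ρ = 0.7 | Type I error |
|---|---|---|---|---|
| 50% / 50%, same selection | 0.80, 0.80 | 0 | 0 | 5% |
| 40% / 60% | 0.97, 0.64 | 0.10 SD | 0.23 SD | about 7% to 16% |
| 30% / 70% | 1.16, 0.50 | 0.20 SD | 0.46 SD | about 12% to 45% |

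If uptake is 50% in both arms but selection runs in opposite directions, the difference is ρ × (0.80 + 0.80), which is 0.48 to 1.12 SD. Equal uptake alone is therefore not reassuring.

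**Range B: a mild symptom-based scenario.** Assume residual symptoms in 15% versus 5.6% of patients, with symptomatic patients twice as likely to agree. Among those sampled:
- 0.15 × 2 / (0.15 × 2 + 0.85) = 0.300/1.150 = 26.1%
- 0.056 × 2 / (0.056 × 2 + 0.944) = 0.112/1.056 = 10.6%

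The symptomatic gap is 15.5 points among those sampled and 9.4 points among those randomised, so selection adds about 6 points. If symptomatic patients differed in fibulin by a full 1 SD (assumed), the added bias is about 0.06 SD. With 33 sampled per arm (half of 66), SE = √(2/33) = 0.246, and a nominal 5% test would reject about 6% of the time.

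The 15% lies within the 12% to 18% short-term recurrence that the Introduction cites for ligation. The 5.6% is the complement of the 94.4% half-year cure rate that the Discussion cites for grade I–III disease. Neither is a month 1 symptom rate, so they only illustrate.

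**The case against.** The strongest reply is that the article gives the time of collection, not the time of agreement. Ethics and registration (2.2) has patients informed of the plan and risks, and signing consent, before the study begins. The full protocol or consent form may already contain a tissue question. This stands as a limit: post-treatment opt-in is the natural reading, not a stated fact.

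Patient blinding narrows the route to bias, since willingness cannot follow knowledge of the arm. It does not close the route through the patient's own symptoms. The mild scenario also shows that the bias could be negligible. That too stands, but nothing in the documents makes the mild scenario more likely than the others.

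A reader might infer several stronger points that the documents do not support:
- *The lack of a baseline sample defeats the comparison.* It does not. With complete sampling, one post-treatment measurement supports a randomised between-arm comparison. The missing baseline matters only because within-patient change cannot be shown and selected groups are harder to check or adjust.
- *Tissue is certainly taken only once.* Item (4) describes one collection, but the word *again* in the limitations paragraph leaves an earlier sample possible.
- *The fibulin comparison is underpowered.* The sample size is based on VAS, and no power is claimed for fibulin.
- *Declining the biopsy ends follow-up.* Nothing says so, and the withdrawal criteria in 2.3.4 do not list it. The authors already disclose that sampling may cause loss to follow-up.

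Finally, agreement at enrolment can be withdrawn at month 1 for the same symptom-related reasons. This is correct, and the fix has to allow for it.

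**Conclusion.** The concern holds in a limited form. As written, the rule allows post-treatment experience to decide who enters the fibulin comparison, and no adjustment is named. A difference could not be safely attributed to treatment. An analysis plan could adjust for measured differences, but it could not restore the randomised comparison once selection has occurred.

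It would go too far to say that no conclusion about fibulin is possible. The bias is plausible, not certain. It is zero if opting in is unrelated to outcome, or if it selects the same kind of patient at the same rate in both arms. Under the assumptions above it runs from about 0.06 SD in the mild scenario to 0.46 SD at 30% versus 70% uptake, and higher if selection runs in opposite directions. No figure within that range can be preferred from the documents.

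The VAS outcome used for sizing is not affected. The change should be made because fibulin is a stated aim and the remedy is cheap.

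**What to change.** 1. Record willingness to give tissue (yes/no) at enrolment, before randomisation. If the full protocol already does this, say so in 2.7.
2. Define the fibulin subset as those who said yes, and analyse it by randomised group.
3. Report uptake and later refusals by arm. Add the baseline characteristics and month 1 symptom status of sampled and unsampled patients, since equal uptake alone does not rule out selection.
4. Complete the month 1 symptom and endoscopy assessment before any tissue is taken, so that symptom status is known for everyone seen.
5. Describe the result as an exploratory between-arm comparison of month 1 expression, not as a demonstrated effect, in the Abstract and in 2.1.
6. Reconcile the word *again* in the limitations paragraph with the single collection in 2.7, item (4).

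The cost is one consent-form item, some wording and a short descriptive table. No extra biopsy and no larger sample are needed. The downside is a weaker mechanistic claim. Some patients who agreed may still refuse at month 1, so residual selection has to be acknowledged when the result is reported.
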